### Intervention and Control Groups

The cancer navigation intervention comprises direct psychosocial and educational webinars, coordinated telephone support services, and community-based cancer care resources offered by professional navigators (Table 1). Professional navigators are qualified registered nurses trained in professional navigation to provide information, connect patients with available supportive services, and help identify information for survivorship. Participants engage in navigator follow-ups, ensuring continuous access to professional guidance.

**Table 1. T1:** Cancer Navigation Reported Outcomes research protocol.

Activity	Protocol	Expectation
1. Recruit eligible participants	Advertisement for participant recruitment: recruit participants by advertisement and poster announcements. When: weekly	Review eligibility criteria to yield eligibility determination. When: at the time of initial participant contact
2. Initial contact by the research team	Cover letter to participants and informed consent form and code of conduct: meet with participants via phone for study information, an introduction, and the baseline survey. When: within 1 week of recruitment or scheduling of the initial appointment	Speak to participants by phone for informed consent and the baseline survey: sociodemographic survey (5 minutes), COST-FACIT^a^ (5 minutes), and FACT-B^b^ (10 minutes) When: within 1 week of initial participant recruitment appointment
3. Communication with the navigator	Participant permission script: communicate with the navigator by email and phone at regular intervals regarding the participant’s enrollment and check-ins. When: within 1 week following randomization	Communicate with the navigator by email and phone at scheduled appointments When: within 1 week following randomization
4. Tracking participants over time	Coordinated telephone support service: meet with participants online based on the schedule. When: within 1 week of randomization	When: (1) at initial intake, (2) within 1 month of randomization, and (3) at the end of each month until completion Speak to a participant by phone at least 6 times during navigation, a total of 12 sessions.

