Participants were randomized to either the cancer navigation intervention or the SOC (the control group). The cancer navigation intervention took place biweekly over 3 months and was facilitated by a professional navigator. The intervention follows tailored approaches to care based on full assessments of participants’ needs and preferences. The intervention includes a full assessment, information and emotional support, and care planning specific to breast cancer survivorship. Professional navigators interact with participants in person during the intervention and follow up with them to provide psychoeducational webinars, telephone helpline support, and cancer care resources (Table 1). The intervention comprises 15 minutes of telephone calls biweekly for 3 months and 6 months, 45 minutes of interactive teaching-learning, a 30-minute webinar, and a 50-minute participant interview, totaling 5 hours (Table 2).

**Table 2. T2:** Schedule of enrollment, trial, and metrics (outcomes) of the intervention and control groups.

	Study period and time point			
	Enrollment (T1), n	Postallocation (T1 at baseline; 0 weeks)	Follow-up (T2 at the end of 3 months; 12 weeks)	Evaluation (T3 at the end of 6 months; 12 weeks)
Enrollment, eligibility screening, informed consent, and randomization allocation	164	^—a^	—	—
Cancer navigation intervention: intervention group	82	—	—	—
Telephone calls	82	6 sessions	6 sessions	—
Interactive teaching-learning	82	2 sessions	2 sessions	—
Interactive webinar	82	2 sessions	2 sessions	—
Standard of care: control group	82	No sessions	No sessions	—
Interview and surveys				
Sociodemographic survey	164	5 minutes	5 minutes	5 minutes
Comprehensive Score for Financial Toxicity–Functional Assessment of Chronic Illness Therapy	164	10 minutes	—	10 minutes
The Functional Assessment of Cancer Therapy–Breast	164	5 minutes	—	5 minutes
Breast Cancer Navigation Survey	164	10 minutes,	—	10 minutes
Participant Satisfaction With Navigation Survey	164	10 minutes	—	10 minutes
Satisfaction With Interpersonal Relationships Survey	164	10 minutes	—	10 minutes
Breast Cancer Navigation Interview	82	—	—	45‐50 minutes

a Not applicable.

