### Data Analysis

All quantitative data will be analyzed using the intention-to-treat principle. Participants who engaged with the study from October 2025 to December 2025 will be included in the analysis.

The FACT-B is the primary measure used to evaluate the effectiveness of professional navigation on health-related QOL. Changes in FACT-B total scores and the scores on its 5 subscales (physical, social, emotional, and functional well-being and the breast cancer subscale) from baseline (T1) to 3 months (T2) and 6 months (T3) will be compared between the cancer navigation intervention and SOC control groups. A repeated-measure ANOVA will be used to determine the interaction between time and the treatment group. A change of 6 to 7 points on the FACT-B is considered clinically significant for this population.

Financial toxicity is an indicator of socioeconomic distress. Financial burden will be quantified using the COST-FACIT instrument. Descriptive statistics will be generated. To determine the impact of financial toxicity on health-related QOL, ANOVAs will be conducted to assess the associations between COST-FACIT scores and health-related QOL outcomes.

The BCNS analyzes participant satisfaction across 13 items to evaluate the user-friendliness and clarity of the program objectives.

The PSNS uses 26 items to measure overall satisfaction with the navigation process. Higher scores will be correlated with secondary outcomes such as treatment adherence using predictive validity testing.

The Satisfaction With Interpersonal Relationships Survey evaluates soft skills and trust in the professional navigator. Discriminant validity will be assessed by distinguishing between technical competence and interpersonal satisfaction scores.

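### The analysis compares FACT-B change at 3 and 6 months, but the schedule table shows no FACT-B at 3 months; one of the two must be corrected

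*Protocol article*

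**What the plan says.** The Data Analysis section states: "The FACT-B is the primary measure used to evaluate the effectiveness of professional navigation on health-related QOL". For the total and the five subscales it plans that changes "from baseline (T1) to 3 months (T2) and 6 months (T3) will be compared between the cancer navigation intervention and SOC control groups". The model is given in the next sentence: "A repeated-measure ANOVA will be used to determine the interaction between time and the treatment group".

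Table 2, under Intervention and Control Groups, is the schedule of assessments. Its 3-month column is headed "Follow-up (T2 at the end of 3 months; 12 weeks"). The FACT-B row reads "The Functional Assessment of Cancer Therapy–Breast 164 5 minutes — 5 minutes": number of participants, baseline, 3 months, 6 months. The dash is footnoted "a Not applicable".

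Table 1 mentions FACT-B once, in the "baseline survey: sociodemographic survey (5 minutes), COST-FACIT^a^ (5 minutes), and FACT-B^b^ (10 minutes"). Recruitment and Data Collection dates a 3-month follow-up to April to June 2025 but names no instrument for it.

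**The concern.** The analysis of the primary measure asks for three FACT-B assessments and the schedule provides two. Anyone following both statements cannot do so: the contrast from baseline to 3 months, for the total and for each subscale, needs scores that the schedule says were not taken.

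The timing adds weight. According to Study Timeline, data collection ended on 30 September 2025 and the study has passed through validation and cleaning, so a missing 3-month FACT-B can no longer be collected. The Results section already reports FACT-B by arm, at 6 months only. If the mismatch stays, a 3-month result that appears later, or one that never appears, could each be read as selective reporting, and the article would give no way to tell.

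**Working it through.** **1. Is the dash really in the 3-month column?** The table was read from a PDF, so alignment has to be checked. The sociodemographic row reads "Sociodemographic survey 164 5 minutes 5 minutes 5 minutes": a count followed by three visit entries. The FACT-B row has the same number of cells, and its dash is in the second of the three visit positions, which is 3 months. The rows for COST-FACIT, the Breast Cancer Navigation Survey, the navigation satisfaction survey and the interpersonal relationships survey show the same pattern. An extraction fault is unlikely.

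**2. Needed against scheduled.**

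| FACT-B assessment | Data Analysis | Table 2 | Elsewhere in the article |
|---|---|---|---|
| T1, baseline | needed | 5 minutes | Table 1, baseline survey |
| T2, 3 months | needed | dash, not applicable | none |
| T3, 6 months | needed | 5 minutes | 6-month results reported |

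Three assessments are needed and two are scheduled.

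**3. What is left if Table 2 is right.** With T1 and T3 only, the time factor has two levels. The time-by-group interaction in a two-level repeated-measures ANOVA is the same test as a two-sample t-test on the change T3 − T1. That test can be run. What is lost is the 3-month contrast and any model with three time levels.

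**4. If only T1 and T3 exist, how do the two usual analyses compare?** This bears on the choice of remedy. It does not measure the effect of the missing visit.

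Inputs: difference 7 points and SD 16.93 (Sample Size and Power); two-sided 5%; 54 completers per arm (Study Timeline). The baseline-to-6-month correlation r is not given, so 0.5, 0.6 and 0.7 are assumptions. The SD is taken as equal at both visits.

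- Variance factor, change score: 2(1 − r)
- Variance factor, T3 adjusted for baseline (ANCOVA): 1 − r²
- Difference: 2(1 − r) − (1 − r²) = (1 − r)², which is never negative, so under these assumptions ANCOVA is at least as precise
- Standard error = 16.93 × √factor × √(2/54); power from the noncentral t distribution with 106 degrees of freedom

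| r | Change: factor | SE | Power | ANCOVA: factor | SE | Power |
|---|---|---|---|---|---|---|
| 0.5 | 1.00 | 3.26 | 57% | 0.75 | 2.82 | 69% |
| 0.6 | 0.80 | 2.91 | 66% | 0.64 | 2.61 | 76% |
| 0.7 | 0.60 | 2.52 | 78% | 0.51 | 2.33 | 85% |

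**5. The article's own figure.** The stated requirement of 108 participants does not follow from a simple comparison of means with its stated inputs: 7 points, SD 16.93, two-sided 5% and 90% power give 123 per arm, 246 in total. That is a separate matter, and the contradiction over the 3-month visit does not depend on it.

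**The case against.** The strongest reply is that Table 2 may be the faulty side. It gives COST-FACIT 10 minutes and FACT-B 5 minutes where Table 1 gives 5 and 10. It labels the 6-month visit as 12 weeks, the same as the 3-month visit. It places satisfaction with navigation at baseline. The article also dates a 3-month follow-up and provides a voucher at baseline and after 3 months, which sits oddly with a visit that collects only a repeat sociodemographic survey. This stands: a table error is a live possibility, and the point cannot assert that 3-month FACT-B data are missing. It does not remove the contradiction, because the published schedule of the primary measure would then be wrong.

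It could also be said that the article condenses a fuller plan. That does not help. The article states both the schedule and the analysis, and no unseen document can make both true.

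Four stronger readings are tempting and are not supported:

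- *The ANOVA cannot be run at all.* It can, on T1 and T3. Only the 3-month contrast and a third time level lack scheduled data.
- *A primary comparison has been lost.* The article calls FACT-B the primary measure but does not label either time contrast as primary.
- *Power was credited to a second follow-up that does not exist.* Sample Size and Power refers to the longitudinal design but gives only a difference, an SD and 25% attrition. It shows no credit for repeated follow-up, and a trial with T1 and T3 is still longitudinal.
- *The power gap in the working is the cost of the missing visit.* It compares two analyses that both use T1 and T3 only, at assumed correlations and in completers, whereas the article specifies intention to treat with 82 randomized per arm.

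**Conclusion.** The contradiction is real and concerns the primary measure: the analysis text requires FACT-B at 3 months and the schedule marks it as not applicable. The documents do not show which statement is correct.

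Its size depends on the answer. If Table 2 is right, one of the two follow-up contrasts, for the total and all five subscales, has no scheduled data in either arm; the 6-month comparison survives. If the analysis text is right, the error is confined to the table and nothing is lost for the analysis.

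Confidence is high in the contradiction itself. The preference for a baseline-adjusted analysis in the two-visit case is about efficiency: the change-score test is valid in a randomized trial, and the gain of about 6 to 12 percentage points of power rests on the assumed correlations of 0.5 to 0.7 and equal SDs at the two visits.

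**What to change.** Check the collected survey records for FACT-B at 3 months, then correct whichever text is wrong.

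- **If FACT-B was collected at 3 months:** correct the FACT-B row of Table 2 and keep the comparisons at T2 and T3. No change of model is needed on this account.
- **If it was not:** delete the 3-month comparison from Data Analysis and state the analysis on the visits that exist. Suggested wording: *FACT-B total at 6 months will be compared between arms by analysis of covariance with baseline FACT-B total as covariate; each subscale will be analysed in the same way with its own baseline score.*

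In the second case the change comes after data collection and after the article itself reported higher 6-month FACT-B means in the intervention arm. It must therefore be dated and disclosed as made with those results known, and the published repeated-measures ANOVA, in its two-visit form, should be reported beside it so that readers can see whether the choice of model matters.

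The cost is a records check and a correction to a table row or a few sentences; no new data are needed. In the second case there is a further cost in credibility, since a post hoc change of model for the primary measure weakens the claim to a prespecified analysis even when the reason is sound.

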### Sample Size and Power

The study is sufficiently powered to detect a clinically meaningful difference while accounting for the longitudinal design. For effect size, the power assumption calculation was based on a minimum clinically significant difference of 7 points on the FACT-B [41]. An estimated SD of 16.93 was used, derived from existing literature on adult survivors of cancer. An attrition rate of 25% was estimated based on the potential for dropout during the 6-month follow-up schedule. While the study is a single-center RCT, the randomization is balanced using blocks of 5 to mitigate potential clustering effects and ensure equal distribution across the 2 arms. With a 5% level of significance (2 tailed) and 90% power, the required sample size was calculated as 108 participants. The total recruitment target is set to 150 participants (75 in the intervention group and 75 in the control group).

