### Functional Assessment of Cancer Therapy–Breast

At the 6-month follow-up, participants in the intervention group demonstrated higher mean scores across all FACT-B domains than the control group. The intervention group reported higher mean scores (mean 25.6, SD 5.2) on the breast cancer subscale than the control group (mean 24.5, SD 7.1; *P*<.01), indicating improved QOL outcomes.

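### The FACT-B analysis treats the collected baseline score as an outcome level instead of a covariate; this is valid but loses precision, by an amount that depends on a correlation the article does not give

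*Protocol article*

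**What the plan says.** The Data Analysis section of the protocol article names FACT-B as the primary measure. Changes in the total and in its five subscales "from baseline (T1) to 3 months (T2) and 6 months (T3) will be compared between the cancer navigation intervention and SOC control groups". The test is then named: "A repeated-measure ANOVA will be used to determine the interaction between time and the treatment group". No baseline covariate appears.

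Baseline FACT-B is available. Table 1, row 2 reads "Speak to participants by phone for informed consent and the baseline survey: sociodemographic survey (5 minutes), COST-FACIT^a^ (5 minutes), and FACT-B^b^ (10 minutes", and Table 2 lists FACT-B at T1. Table 2 shows it again only at 6 months, with a dash at 3 months, although Data Analysis plans a change to T2.

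Sample Size and Power rests on a "minimum clinically significant difference of 7 points on the FACT-B". It adds: "An estimated SD of 16.93 was used, derived from existing literature on adult survivors of cancer". It does not say whether that SD belongs to a single score or to a change, and it states no correlation between visits.

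**The concern.** When baseline is one level of a repeated-measures outcome, the time-by-group interaction compares unadjusted changes. A change score fixes the slope on baseline at 1. ANCOVA estimates that slope, which is normally below 1, and so leaves less residual variance. A change score also over-corrects for any chance baseline difference between arms, through regression to the mean.

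At stake is precision that data already in hand would supply. The trial has 54 completers per arm, and its stated inputs call for more than twice that number.

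**Working it through.** **Inputs from the article.** Difference 7, SD 16.93, two-sided 5% (Sample Size and Power); 54 completers per arm out of 82 randomised (Study Timeline); FACT-B at T1 and T3 (Table 2).

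**Assumed.** Rho, shown from 0.3 to 0.8, and equal variance at both visits.

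**The plan's own figure.** The article says: "With a 5% level of significance (2 tailed) and 90% power, the required sample size was calculated as 108 participants". An unadjusted comparison of two means needs, per arm, 2 × (1.960 + 1.282)² × 16.93² / 7² = 122.9, so 123 per arm and 246 in total. The 108 does not reproduce. It appears only with an unstated correlation: about 0.75 with ANCOVA, or about 0.78 with change scores.

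**Variances, two visits.** With T1 and T3 only, the time-by-group interaction is the two-sample t-test on change.
- Change: 2σ²(1 − rho)
- ANCOVA: σ²(1 − rho²)
- Ratio, ANCOVA to change: (1 + rho)/2, which is below 1 for every rho below 1

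At rho 0.5 the change SD is 16.93 × √1 = 16.93 and the ANCOVA SD is 16.93 × √0.75 = 14.66.

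**Power at 54 per arm** (noncentral t; 106 df for change, 105 for ANCOVA).

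If 16.93 is the raw-score SD:

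| rho | SD of change | ANCOVA SD | Change | ANCOVA | Loss (points) |
|---|---|---|---|---|---|
| 0.3 | 20.03 | 16.15 | 43.6% | 60.7% | 17.1 |
| 0.5 | 16.93 | 14.66 | 56.7% | 69.1% | 12.4 |
| 0.7 | 13.11 | 12.09 | 78.5% | 84.6% | 6.2 |
| 0.8 | 10.71 | 10.16 | 92.0% | 94.4% | 2.4 |

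If 16.93 is the SD of change, the ANCOVA SD is 16.93 × √((1 + rho)/2) and change-score power stays at 56.7%:

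| rho | ANCOVA SD | ANCOVA | Loss (points) |
|---|---|---|---|
| 0.3 | 13.65 | 75.2% | 18.5 |
| 0.5 | 14.66 | 69.1% | 12.4 |
| 0.7 | 15.61 | 63.6% | 6.9 |
| 0.8 | 16.06 | 61.2% | 4.5 |

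Losses are taken from unrounded powers.

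**All 82 per arm, raw-score SD.** The loss is 11.1 points at rho 0.5 (74.9% v 86.0%), 3.3 at 0.7 and 0.6 at 0.8.

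**Three visits.** If T2 is also measured, the interaction is a 2-df F test. At 54 per arm, rho 0.5 between all visits and raw-score SD, arm differences of 0, 7, 7 give noncentrality 6.15 and power 58.9%. Differences of 0, 3.5, 7 give 4.62 and 46.5%. ANCOVA at T3 has 69.1% in both cases, so the loss is about 10 or 23 points depending on the time pattern.

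**The case against.** **It is a valid method, and an unseen analysis plan may add covariates.** Validity stands: under randomisation the interaction test is unbiased, and a reader who inferred bias from this choice would go too far. Silence on covariates would be no finding either. But the article does more than stay silent: it names the model and puts baseline inside the outcome.

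**The loss cannot be quoted as a fixed 12 points.** This stands. That figure needs rho 0.5, which the article does not give. At the correlations that would make 108 give 90% power (about 0.75 to 0.78, raw-score SD), the loss is only 3 to 4 points.

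**54 per arm is not a stated analysis set.** This stands. These are completers, and Data Analysis plans intention to treat.

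**The t-test equivalence belongs to Table 2, not to Data Analysis.** This stands. It holds for two visits; Data Analysis names three, and then the pattern over time matters too.

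**The reported results might seem to show a rival unadjusted contrast.** The Results section says "At the 6-month follow-up, participants in the intervention group demonstrated higher mean scores across all FACT-B domains than the control group", and a reader might infer that raw 6-month means were tested without baseline. The article does not support this. No test is named, and the printed breast cancer subscale figures (25.6, SD 5.2 v 24.5, SD 7.1, taking 54 per arm) give a standard error of √((5.2² + 7.1²)/54) = 1.20, t = 1.1/1.20 = 0.92 and P = 0.36, against the printed P<.01. The source of that P value cannot be identified.

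**Changing the primary analysis now invites a charge of selection.** This is fair, because arm comparisons have already been reported. It governs how the change must be made and does not remove the reason for it.

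**Conclusion.** The point holds as one of efficiency. The stated FACT-B analysis is less precise than a baseline-adjusted one for every rho below 1, apart from one degree of freedom. Only the size of the loss is uncertain. At 54 completers per arm with two visits it is about 2 to 17 points of power over rho 0.8 to 0.3 if 16.93 is a raw-score SD, and about 4.5 to 18.5 points if it is a change SD. All these figures rest on an assumed rho.

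Adjustment does not rescue the sample size. At rho 0.5 and 54 per arm, ANCOVA reaches 69%, against the planned 90%. That 108 does not follow from its stated inputs is a separate and larger problem.

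**What to change.** In Data Analysis, state that the between-arm difference in FACT-B total at 6 months will be estimated by a linear model (ANCOVA) with treatment group and baseline FACT-B total, and reported as an adjusted mean difference with a 95% confidence interval. Analyse each subscale in the same way with its own baseline.

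Reconcile Table 2 with Data Analysis on whether FACT-B was taken at 3 months. If it was, use a repeated-measures model of the post-baseline visits with baseline as covariate and the 6-month contrast as the main estimate. State the baseline-to-follow-up correlation, and say what the SD of 16.93 refers to.

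The cost is one degree of freedom, a short edit and a re-run on existing data. The real cost is timing. Between-arm results are already in the article, so the change must be dated, disclosed as made after data were seen, and reported alongside the originally stated ANOVA.

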### Data Measurement Instruments and Outcomes

The main outcomes are financial distress; QOL, such as physical, social, emotional, and functional well-being; and satisfaction with navigation and interpersonal relationships, measured using the instruments outlined in this section.

A sociodemographic survey is used to collect the demographics of the participants.

The COST-FACIT was developed by de Souza et al [36] in conjunction with the University of Chicago and is a patient-reported outcome measure that describes the financial distress experienced by patients with cancer.

The FACT-B is a 37-item instrument designed to measure 5 domains of health-related QOL in patients with breast cancer: physical, social, emotional, and functional well-being and a breast cancer subscale. The FACT-B was developed with an emphasis on patients’ values and brevity [37].

The Breast Cancer Navigation Survey (BCNS) comprises 10 items on a 5-point rating scale from “very dissatisfied” to “very satisfied” and 3 items on a 3-point rating scale from “very dissatisfied” to “very satisfied” [38]. This survey takes 10 minutes to complete (Multimedia Appendix 1).

The Participant Satisfaction With Navigation Scale (PSNS) has 26 items on a 5-point rating scale, from “very satisfied” to “do not know” or “refuse to answer,” was developed by a multidisciplinary team of researchers and clinicians from the National Cancer Institute (NCI)–sponsored Patient Navigation Research Program, led by Jean-Pierre [39]. This survey takes 10 minutes to complete.

The Satisfaction With Interpersonal Relationships Survey comprises 10 items on a 5-point rating scale from “very dissatisfied” to “very satisfied” and 3 items on a 3-point rating scale from “very dissatisfied” to “very satisfied” [40]. This survey takes 10 minutes to complete.

The Breast Cancer Navigation Interview includes 10 questions on perspectives on diagnosis, treatment, and navigation (Multimedia Appendix 2).

Internal consistency reliability for the COST-FACIT for participants diagnosed with breast cancer using Cronbach α for the 2-factor structure was 0.76 to 0.82. A pretest with 30 female patients with breast cancer found a mean COST-FACIT score of 21.23 (SD 9.85). Construct validity for the COST-FACIT score correlated negatively with higher psychological distress and positively with better QOL and lower out-of-pocket costs.

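### Relating COST-FACIT to QOL by ANOVA suits two numeric scores poorly, and the word impact claims more than this observational association can support

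*Protocol article*

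**What the plan says.** The Data Analysis section of the protocol article sets the aim as "To determine the impact of financial toxicity on health-related QOL" and then states that "ANOVAs will be conducted to assess the associations between COST-FACIT scores and health-related QOL outcomes". The sentence does not say which score is the factor, which is the response, or which visits are paired.

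Both instruments are treated as numeric elsewhere:

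- **COST-FACIT.** Data Measurement Instruments and Outcomes summarises it by a mean and SD: "A pretest with 30 female patients with breast cancer found a mean COST-FACIT score of 21.23 (SD 9.85").
- **FACT-B.** Data Analysis works with "Changes in FACT-B total scores and the scores on its 5 subscales".

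Table 2 (Intervention and Control Groups) schedules COST-FACIT and FACT-B at baseline (T1) and 6 months (T3), with neither at 3 months (T2). Data Analysis also refers to FACT-B at T2. That mismatch is a separate matter and this point does not rest on it.

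**The concern.** Two things in the sentence do not fit together.

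**Method and data.** ANOVA in its ordinary sense compares the mean of a numeric response across categories. With a numeric score on each side, one must be cut into groups before it can serve as the factor. Grouping treats everyone within a band as alike, which discards information and lowers power. It also replaces a slope, which is easy to interpret, with differences between bands.

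**Aim and design.** The aim speaks of impact, while the analysis assesses association. Participants are randomised to navigation or standard care, not to a level of financial toxicity. Poorer health may raise financial strain just as strain may lower QOL. Navigation could also move both scores, so a pooled association at 6 months that ignores arm could partly reflect the intervention.

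Financial distress is the first of the main outcomes listed, and this is the only inferential use of COST-FACIT that Data Analysis describes. At stake are the precision and the interpretation of that one result.

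**Working it through.** The article gives no figure for this analysis, so there is none to reproduce. The size of the loss can only be illustrated.

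**Inputs**

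- n = 108 completers, 54 per arm (Results, Study Timeline). At baseline n = 164.
- Two-sided 5% level. The article states this for its sample size, and it is borrowed here.
- Correlation r between COST-FACIT and FACT-B: not given. Assumed 0.2, 0.3 and 0.4.
- Bivariate normal scores: assumed.
- Grouping: not given. A median split is the main illustration, with tertiles and a 20/80 cut for range.

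**Step 1: information kept by one cut.** With a share p below the cut c, the fraction of explained variance kept is φ(c)² / [p(1 − p)], where φ is the standard normal density.

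- Median split: 0.3989² / 0.25 = 0.637, or 2/π. So 108 people carry the information of about 108 × 0.637 = 69.
- 20/80 cut: 0.49.
- Tertiles (three-group version of the formula): 0.79.

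**Step 2: power by Fisher's z, n = 108.** Power ≈ Φ(atanh(r) × √(n − 3) − 1.96), with √105 = 10.25. A median split multiplies r by √0.637 = 0.798.

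- r = 0.2: continuous 0.2027 × 10.25 = 2.08, power 55%. Split r = 0.160, 0.161 × 10.25 = 1.65, power 38%.
- r = 0.3: continuous 0.3095 × 10.25 = 3.17, power 89%. Split r = 0.239, 0.244 × 10.25 = 2.50, power 71%.
- r = 0.4: continuous 0.4236 × 10.25 = 4.34, power 99%. Split r = 0.319, 0.331 × 10.25 = 3.39, power 92%.

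**Step 3: simulation.** In 3,000 data sets per setting, a linear test on the continuous score was compared with one-way ANOVA on the grouped score (n = 108):

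| Assumed r | Continuous | Median split | Tertiles | 20/80 cut |
|---|---|---|---|---|
| 0.2 | 56% | 39% | 37% | 31% |
| 0.3 | 88% | 70% | 71% | 58% |
| 0.4 | 99% | 93% | 94% | 85% |

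The first two columns agree with Step 2 to within about a percentage point. With all 164 at baseline, continuous against median split is 75% against 53% at r = 0.2, 98% against 89% at 0.3, and 100% against 99% at 0.4.

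**Limits.** These figures are for a simple two-variable association. They do not carry over to a model that adjusts for baseline FACT-B. If the ANOVA was meant as the F test of a linear model with a continuous predictor, the loss is zero.

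**Aim against analysis.** The two halves of the sentence use different terms. The second, association, is the one that the design supports.

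**The case against.** The strongest reply is that the sentence is loose rather than wrong. It does not make COST-FACIT the factor: QOL could be the grouped variable, or ANOVA could be shorthand for the F test of a regression. The sentence itself already calls the analysis one of associations, the analysis is secondary, and an article may leave such detail to an analysis plan that is not shown. All of this is fair, and it limits the point to the method named and the word impact.

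A reader might go further in three ways that the document does not support:

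- **That the plan forces a COST-FACIT cut-off.** It does not, for the reasons just given. The absence of a cut-off from the article is no finding, since it may stand in the full plan.
- **That the scores are compared at the same visit, so time order cannot be examined.** Table 2 shows when the instruments are given, not how they are paired. COST-FACIT at T1 and FACT-B at T3 are both scheduled, and the text neither uses nor excludes that pairing.
- **That the false-positive rate exceeds 5%.** This would need a cut-off chosen after seeing the data, and nothing in the article says that one was or will be.

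What remains is that the article names a method which, on its ordinary reading, is inferior for two numeric scores. The document's own usage favours that reading: Data Analysis uses repeated-measures ANOVA to compare the treatment groups, and speaks of correlation when it relates satisfaction scores to other outcomes. If a regression was meant, the article should say so. On either reading, impact is too strong.

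**Conclusion.** The point holds at low severity. As worded, the analysis is a poor match for two numeric scores, and its stated aim exceeds what an observational association between two patient-reported scores can show.

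If one score is grouped, 49% to 79% of the explained variance is kept for the groupings considered. With 108 completers, a median split costs about 17 points of power at r = 0.2 (56 − 39), 18 at r = 0.3 (88 − 70) and 6 at r = 0.4 (99 − 93). This rests on an assumed correlation, approximate normality and an assumed grouping, none of which the document gives. If a continuous-predictor model was intended, only the wording needs to change.

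The primary randomised comparison of FACT-B between arms is untouched.

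**What to change.** - **Method.** Replace the ANOVAs with a linear model of FACT-B on continuous COST-FACIT, adjusted for arm, or with a mixed model if more than one visit per participant is used. State which visits are paired.
- **Reporting.** Give the FACT-B difference per 10 COST-FACIT points (about one SD, given the pretest SD of 9.85) with its 95% CI, and check linearity, for example with a spline.
- **Wording.** Replace impact with association in the aim of this analysis.
- **Optional addition.** Fit T3 FACT-B on T1 COST-FACIT, adjusted for T1 FACT-B and arm. This asks a narrower question: whether baseline financial toxicity predicts later QOL, given baseline QOL. It adds time order but shows prediction, not causation.

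**Cost.** A few words and one regression on data already collected, with no new measurement. The small downside is the linearity assumption, which the spline addresses. The change can be made before the results are published, which the article expects in December 2026.
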